#### Pharmaceutical administration

##### Drug delivery of modern medicine

Each subject will be administered modern medicine (pirfenidone, acetylcysteine, or glucocorticoid), irrespective of the group they have been assigned to.

##### Dispensing the herbal medication

Each center will have a drug administrator who is responsible for the storage, distribution, recovery, record keeping, and retrieval of the experimental drugs. The modern medicine + TCM or modern medicine + TCM placebo will be provided to patients based on the enrollment sequence. The modern medicine + TCM or modern medicine + TCM placebo administered to patients will remain unchanged throughout the study. The test drugs will be distributed in each follow-up after the beginning of the study, and the leftover drugs will be recovered in the next drug allocation.

##### Subject compliance and drug inventory

During the trial, patient compliance will mainly be centered around ensuring drug intake based on the advice of the physician or the drug administrator. Measures will be taken to ascertain that each subject adequately understands the importance of medicating. They will also be educated to ensure that the dosage instructions are appropriately followed and they prevent the concurrent use of other drugs or treatment methods during the study period.

The physician in charge will be trained to count and recover the remaining drugs from patients during follow-up and will be educated to ask questions on whether the subject has taken the prescribed dose of the medication. The attending physician will be trained to record information in cases of missed or insufficient doses and present the information as a case report form (CRF), which will be used to determine patient compliance.

### Outcomes

#### Primary outcome

The main outcome measure is the treatment effect, which will measure the classification indicators, such as improvement, stabilization, and deterioration levels. This three-level classification will monitor changes in TLC, VC, DLCO, SaO_2,_ and PaO_2._ The specific classification criteria will be as follows:

Improvement: after treatment of subjects, an increase in the TLC or VC by 10%, an increase in DLCO by 15%, an increase in SaO_2_ by 15%, and an increase in PaO_2_ by 4 mm Hg (1 mmHg = 0.133 kPa), compared to the pre-treatment values.

Stabilization: the health status of subjects between improvement and deterioration.

Deterioration: after treatment of subjects, a decrease in the TLC or VC by 10%, a decrease in DLCO and SaO_2_ by 15%, and a decrease in PaO_2_ by 4 mm Hg (1 mmHg = 0.133 kPa), compared to the pre-treatment values.

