##### Sample size calculation

For dichotomous variable and superior clinical design, the sample size was determined using the following formula to calculate the sample size [29, 30, 31]:

$$N = 2 \times \left( {\frac{{Z_{1 - \alpha } + Z_{1 - \beta } }}{{d - \delta_{0} }}} \right)^{2} \times p \times (1 - p)$$,

where the null hypothesis H_0_: T–S = δ;

the alternative hypothesis H_1_: T–S > δ;

And test statistics: Z = (d–δ)/sd.

In the equation, N represents the size of the group. p indicates the response rate of the control group and p_0_ denotes the response rate of the treatment group. Z_x_ represents the normal standard deviation for a one- or two-sided x. d represents the real difference between the two treatment effects. δ_0_ indicates a clinically acceptable margin. S^2^ indicates the pooled standard deviation of both comparison groups. T represents the treatment group (modern medicine + TCM treatment). S is the control group (modern medicine + TCM placebo). δ indicates the clinically admissible margin of superiority. d represents the effectiveness difference between T and S (d =| p_0_—p |). sd represents the standard error of d. Z = Z obeys the normal standard distribution. α represents type I error, β represents type II error, and 1 − β indicates the power.

In this study, α = 0.05, β = 0.20, δ_0_ = 0.10, 1 − β = 0.80, Z_1−α_ = 1.64, Z_1−α_ = 1.28, and based on literature, *P*_0_ = 0.767 and *P* = 0.533[29]. Hence, a value of *N* = 233 was calculated. The failure to follow-up rate was considered to be 10% and accordingly, *N* = 233 × (1 + 10%) = 257. Lastly, the number of subjects each in the treatment and control groups is 257, which led to a total of 514 individuals in this study.

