##### Inclusion criteria

Patients who meet all the following inclusion criteria may be included in the clinical trial:Diagnostic criteria for severe or critical COVID-19Patients exhibiting positive etiological evidence of the SARS-CoV-2 nucleic acid determined using real-time polymerase chain reaction (PCR) or gene sequencing will be included. In addition, patients should meet at least one of the following diagnostic criteria of severe COVID-19. First, shortness of breath and a respiratory rate (RR) ≥ 30 times/min. Second, oxygen saturation (SpO_2_) in quiescent condition ≤ 93% using finger measurement. Third, arterial partial pressure of oxygen (PaO_2_)/oxygen inhalation concentration (FiO_2_) ≤ 300 mmHg (1 mmHg = 0.133 kPa). The PaO_2_/FiO_2_ will be recalculated when patients will be enrolled from regions at high altitudes, especially those located 1000 m above sea level, using the following formula: PaO_2_/FiO_2_ × [atmospheric pressure (mmHg) /760].The diagnostic criteria of critical COVID-19 should meet one of the following criteria, including respiratory failure and those who needed mechanical ventilation, shock, or respiratory failure combined with organ failure, which required monitoring and treatment in an intensive care unit (ICU).Diagnostic criteria for pulmonary fibrosisThe diagnosis criteria of pulmonary fibrosis will be in accordance with the guidelines of evidence-based medicine (2011 Edition) of the ATS, European Respiratory Society (ERS), Japanese Respiratory Society (JRS), and the Latin American Thoracic Association (ALAT).The inclusion criteria for patients with pulmonary fibrosis should meet one of the following conditions. First, subjects should present diffuse, asymmetric reticular formation in the lungs. Second, the reticular formation should show nodular shadows in a lung X-ray and there should be reticular shadows in the lower lobes of both lungs, especially under the pleura. Third, subjects should exhibit restrictive ventilation dysfunction, decreased lung volume, functional residual volume, and normal or increased forced lung volume (FLV)/ forced expiratory volume in 1 s(FEV1) upon assessing lung function. In addition, they should exhibit decreased carbon monoxide(CO) levels exhaled in the single-breath determination of CO. Open chest or thoracoscopic lung biopsy will be considered the “gold standard" for the diagnosis of pulmonary fibrosis.In this study, the pulmonary function indices must meet the following criteria. First, the predicted forced vital capacity (FVC%) must be between 50 and 90%. Second, the diffusion capacity for carbon monoxide (DLCO) should be between 30 and 90%. Third, the FEV1/forced vital capacity(FVC) must be over 80%. Fourth, when subject is at rest in a room and is respiring normally, the oxygen partial pressure should more than 50 mmHg.TCM syndrome differentiation for subjectsThe criterion of TCM syndrome differentiation complies with TCM disease diagnosis and efficacy standards promulgated by the China State Administration [32]. In addition, the criterion of Qi-Yin deficiency must meet the following criteria, including shortness of breath, cough, sputum expectoration, a small amount of yellow and white sputum, spontaneous sweating, night sweats, fatigue, drawl, dry mouth, afternoon hot flashes, hot facial flashes, anorexia, red tongue, thin white coating on the tongue, and weak pulse[32]. Qi-Yin deficiency was found to account for 41.5% (39/94) of all individuals with pulmonary fibrosis in other studies[33].Age: ≥ 18 yearsWritten informed consent must be obtained from the patient or from their legal guardian. Patient may also be enrolled upon confirmation of the urgency of participation in the clinical trial and the possible benefit to the patient assessed by an independent consultant, or the implementation of other established procedures to include patients who are unable to provide informed consent.

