
##### Exclusion criteria

Patients who meet any of the following exclusion criteria will be excluded from this trial. First, diagnosis of any lung diseases, such as bronchiectasis, tuberculosis, bronchial asthma, chronic obstructive pulmonary disease (COPD), dyspnea, respiratory failure, lung cancer, or those with a history of these diseases. Second, patients with a status of acute exacerbation of pulmonary fibrosis. Third, patients with severe disorders of the cardiovascular system, nervous system, and digestive system; serious mental diseases, tumors, human immunodeficiency virus (HIV) infection/acquired immune deficiency syndrome (AIDS), tuberculosis, autoimmune diseases, and severe liver and kidney dysfunction. Fourth, patients who received glucocorticoids, immunosuppressants, and other drugs for treatment of pulmonary fibrosis or other diseases in the past 3 months. Fifth, participation in another interventional clinical trial within the past 3 months. Sixth, patients who did not provide informed consent. Finally, lactating women will be excluded from the study.

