#### Data analysis of the main outcome measure

The main outcome measure is treatment effect, and this categorical variable includes improvement, stabilization, and deterioration. Stabilization and deterioration will be merged into a new variable, namely non-improvement. Hence, this three-level classification will comprise merged binary variables and include improvement and non-improvement. For this dichotomous variable, Breslow-Day method, CMH, GEE, and logistic regression will be utilized to compare curative effects between the two groups.

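### As written, Improvement needs a 15% rise in SaO2 that no patient starting above about 87% can reach, and this does not fit the planned response rates of 53.3% and 76.7%

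*Protocol article*

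**What the plan says.** The Primary outcome section of the protocol article sets three classes. Improvement begins with "an increase in the TLC or VC by 10%, an increase in DLCO by 15" percent and continues with "an increase in SaO_2_ by 15%, and an increase in PaO_2_ by 4 mm Hg", all against pre-treatment values. The only 'or' lies between TLC and VC. The other items form a comma list closed by 'and' ("an increase in DLCO by 15%, an increase in SaO_2_ by 15%, and an increase in PaO_2"), and nothing says that any one of them is enough. The unit of the SaO2 change (relative percent or percentage points) is not stated. Deterioration mirrors the list with falls, and Stabilization is whatever lies between.

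The section on analysis of the main outcome then makes the comparison binary: "Stabilization and deterioration will be merged into a new variable, namely non-improvement". The primary comparison is therefore Improvement against everything else.

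On baseline oxygenation, the Inclusion criteria say that at rest "the oxygen partial pressure should more than 50 mmHg". The Sample size calculation plans on response rates of 0.767 (treatment) and 0.533 (control).

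**The concern.** SaO2 has a ceiling of 100%, and a required gain of 15% uses up most of the room that an eligible patient could have. A patient who starts above the level from which the gain is possible can never be classed as improved, however much TLC, VC, DLCO and PaO2 rise. If most patients are in that position, the primary endpoint cannot register a benefit in them, and a 514-patient, 12-month trial would rest on a small remainder. Response rates of 53.3% and 76.7% would also not belong to the endpoint as defined.

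**Working it through.** **Inputs.** Limbs and thresholds: Primary outcome. PaO2 floor of 50 mmHg: Inclusion criteria. Rates 0.533 and 0.767, margin 0.10, Z values 1.64 and 1.28, 233 per arm: Sample size calculation. Two-tailed test at 0.05: Principles of data analysis.

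**1. The plan's own figure.** N = 2 × ((1.64 + 1.28)/(0.234 − 0.10))² × 0.533 × 0.467 = 2 × (2.92/0.134)² × 0.2489 = 236.4, against the stated 233. The figure is reproduced to within 2%, so the rates 0.533 and 0.767 do drive the sample size. (Z = 1.28 corresponds to 90% power, not the stated 80%. That is a separate matter.)

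**2. The SaO2 ceiling.** This step needs no outside data.
- Relative reading: baseline × 1.15 ≤ 100, so baseline ≤ 100/1.15 = 86.96%.
- Percentage-point reading: baseline + 15 ≤ 100, so baseline ≤ 85%.
- A patient at 90% would need 103.5% or 105%.

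**3. What this means for planning.** Response cannot exceed the share of patients able to meet the limb. A rate of 76.7% on treatment requires at least 76.7% of that arm to start at or below 86.96%. A rate of 53.3% on control requires at least 53.3% of that arm to do so.

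**4. Who can meet the limb.** Assumption: the standard oxygen dissociation curve in the form S = 100/(23400/(P³ + 150P) + 1).

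| PaO2 (mmHg) | SaO2 (%) | SaO2 × 1.15 (%) |
|---|---|---|
| 50 | 85.0 | 97.7 |
| 52.9 | 87.0 | 100.0 |
| 60 | 90.6 | 104.2 |
| 80 | 95.7 | 110.1 |

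On the relative reading, only a baseline PaO2 of about 50 to 53 mmHg leaves room, and those patients must finish at about 98 to 100%. On the point reading the limit (85%) coincides with the eligibility floor, so essentially nobody qualifies.

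**5. Effect on power.** The baseline SaO2 distribution is not given. Let f be the share of patients able to meet the limb, and assume that the planning rates apply within that share. The rates become 0.533f and 0.767f. With n = 233 per arm, a two-sided 0.05 test and no margin, power = Φ((d − 1.96·SE0)/SE1), where d is the difference in rates, SE0 = √(2p̄(1 − p̄)/n), p̄ is the mean of the two rates, and SE1 = √((p₁(1 − p₁) + p₂(1 − p₂))/n).

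| f | Control | Treatment | Expected responders (control, treatment) | Power |
|---|---|---|---|---|
| 1% | 0.5% | 0.8% | 1.2, 1.8 | 5% |
| 5% | 2.7% | 3.8% | 6.2, 8.9 | 11% |
| 10% | 5.3% | 7.7% | 12.4, 17.9 | 17.5% |
| 20% | 10.7% | 15.3% | 24.8, 35.7 | 32% |
| 100% | 53.3% | 76.7% | 124.2, 178.7 | >99.9% |

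For example, at f = 10%: d = 0.0234, SE0 = 0.02284, SE1 = 0.02281, and (0.0234 − 0.04477)/0.02281 = −0.937, which gives 17.5%.

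A true difference above the plan's own 10-point margin would need f > 0.10/0.234 = 43%.

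**6. The alternative reading.** If any one limb were enough, a patient with DLCO up 15% and PaO2 down 4 mmHg would be both improved and deteriorated. No precedence rule settles this.

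**The case against.** The strongest objection concerns intent. The list says neither 'all of' nor 'any of', and planning rates of 53.3% and 76.7% fit a requirement to meet every limb so poorly that the authors may have meant something looser. Under an any-one-limb rule, the SaO2 ceiling would not hold the response rate down. This stands as a caution about what was meant, but not as a defence of the text. The closing 'and' makes the joint requirement the natural reading, no looser rule is stated, and the looser rule creates the overlap in step 6. A precedence rule or a stated number of limbs could remove that overlap, so requiring every limb is not the only acceptable remedy.

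A second objection is that baseline saturation is not reported. That also stands. A reader might infer that the response rate must be about zero in both arms and that power falls to the false-positive rate. The documents do not support that as a point claim. The window is narrow but not empty, and power near 5% belongs only to the bottom of the range (f about 1%).

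Third, one might argue that the exclusion of respiratory failure ("dyspnea, respiratory failure, lung cancer, or those with a history of these diseases") removes the remaining low-saturation patients. It is weak support, because the Inclusion criteria admit critical COVID-19 defined partly by respiratory failure. The argument here uses only the PaO2 floor.

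Finally, the source of the planning rates is not at hand, so one can call them implausible for this endpoint as written, but not shown to be wrong.

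**Conclusion.** The point holds for the rule as written. The ceiling of 86.96% (relative) or 85% (points) is pure arithmetic. That most eligible patients lie above it is an inference from the PaO2 floor and a standard dissociation curve. On that basis most patients are non-improved regardless of benefit, and the planning rates do not fit the endpoint. The size is a range: power of about 5% to 32% if 1% to 20% of patients can meet the limb. Even that is generous, since it lets the planning rates apply among those patients although they must finish near full saturation. The power figures use the two-sided test without the margin.

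This needs correcting, because it concerns the definition of the primary endpoint. Confidence is high in the arithmetic and lower in any single response rate or power figure.

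**What to change.** In both Improvement and Deterioration, either drop the 15% SaO2 limb or replace it with a threshold, in a stated unit, that is attainable from the baseline values that eligibility allows. Dropping it would still leave PaO2 as a measure of oxygenation, but the choice is the sponsor's. Write each threshold as 'at least'. State the combination rule explicitly, so that the three classes are mutually exclusive.

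Then restate the planning response rates and the resulting power for the revised definition. The remaining limbs, if all are required, are still demanding, and nothing in the article shows that they would yield 53.3% or 76.7%. Do this before enrolment, or before unblinding if enrolment has begun.

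The cost is protocol wording and a repeat of the sample size calculation, which may change the number of patients. No new measurement is needed.

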#### Secondary outcome measure

*(1) Indices reflecting respiratory function*

Certain variables will be monitored for each subject during every follow-up, including VC, TLC, FVC, FVC%, DLCO, DLCO%, FEV1, RV, MVV, RV/TCL, ERV, IRV, PEF, MMEF, VT, and IC.*(2) Six-minute walking distance and Borg dyspnea score*

The quantitative variable of 6-min walking distance and the Borg dyspnea score will be obtained for each subject in each observation.*(3) Quality of life assessment indices*

The SCL-90, SF-36, SAS, and SDS scales will be used to collect the score (quantitative variable) for each subject during each visit.*(4) Evaluation standard of treatment effect in TCM syndrome*

The treatment effect in TCM syndrome will be divided into four categories based on the guiding principles for clinical research of the new TCM (Trial) (2018 year). The categorical variables are clinical cure, notable effect, effective, and ineffective. The specific classification criteria are as follows:

Clinical cure: a reduction rate of TCM syndrome scores ≥ 95%;

Notable effect: a reduction rate of TCM syndrome scores to between 70 and 95%.

Effective: a reduction rate of TCM syndrome scores to between 30 and 70%.

Ineffective: a reduction rate of TCM syndrome scores < 30%.

The reduction rate of TCM syndrome scores(%) = (pre-treatment TCM syndrome scores-post-treatment TCM syndrome scores) / TCM syndrome scores × 100%

The total effective rate(%) = (clinical cure cases + notable effect cases + effective cases) / total cases × 100%.

The data will be analyzed to determine if there are significant differences between the treatment and control groups after treatment, if there are significant differences in the treatment group pre- and post-treatment, and if there are significant differences in the control group pre- and post-treatment.

#### Safety indices

It is necessary to pay close attention to any changes in the relevant safety indicators during treatment as certain therapeutic drugs (especially herbs) may cause organ damage. The safety indices include body temperature, blood pressure, heart rate, respiration, height, and weight, among others[37] (Table 2). Upon and after recruitment, the safety indices of all subjects will be determined several times during the 12-month treatment procedure.

**Table 2 Tab2:** Safety indexes will be detected for each volunteer in the study

Classification	Index	Detection time point
Blood routine	Red blood cell, hemoglobin, white blood cell, white blood cell classification count, hematocrit, platelet, etc	When one volunteer will be recruited, these safe indexes will be detected for five times (0 month, 3rd month, 6th month, 9th month, 12th month) across whole study
Urine routine	PH, urine specific gravity, urobilinogen, urine blood, white blood cell, urine protein, glucose in urine, bilirubin, ketone body, urine red blood cell, etc	
Liver function	Total protein, globulin, albumin, alanine aminotransferase, aspartate aminotransferase, total bilirubin, direct bilirubin, indirect bilirubin, urine bilirubin, urobilinogen, serum bile acid, gamma glutamyltranspeptidase, alkaline phosphatase, etc	
Kidney function	Serum urea, uric acid, blood β-microglobulin, serum creatinine, etc	
Blood sugar	Fasting blood sugar	
Electrocardiogram	Chest leads, limb lead	

*PH* hydrogen ion concentration

### Participant withdrawal

Participation in this clinical trial is voluntary. All subjects have the right to withdraw their consent prematurely from the trial, at any time and without stating reasons, and without incurring any setbacks for their future medical treatment. Withdrawal of consent will automatically lead to the disqualification of the patient. No further study-related measure will be carried out. However, the stored data may continue to be used, as deemed necessary, to determine the effects of the intervention.

### Suspension of protocol

Participation of a patient in the clinical trial may be prematurely terminated under the following circumstances: (1) death of the participant, (2) failure to obtain consent to the continuation of the clinical trial, and (3) refusal to continue the clinical trial by formerly incapacitated patients who have regained their ability to provide consent.

The principal investigator have the power to pause or terminate the clinical trial in a trial center in coordination with the Safety Committee and the biometrician for a number of reasons. These include if (1) serious safety problems occur during the study period. (2) The drug efficacy is found to be poor or ineffective midway during the study. 3) Major errors or flaws are detected in the trial design. (4) The research team requests the termination of the study for reasons including, but not limited to, funding, management, or a lack of study subjects for recruitment. (5) The administrative department cancels the study.

### Data management and monitoring

#### Principle

Experimental data will be carefully entered into an electronic CRF. To guarantee data quality, we will appoint a research assistant who will be responsible for quality control during data collection. Participant identity and sensitive information will be deleted from all study documents to protect patient confidentiality. All outcomes will be double-checked manually and a second independent data entry will be conducted to promote data quality. Following data entry, only the personnel directly involved in data analysis will be granted access to the final trial datasets. During the study, an independent data and safety monitoring board of the Global Health Center of Shanghai Jiao Tong University will be responsible for monitoring the safety, progress, study integrity, and design aspects of the trial. Dropouts and withdrawals will be recorded throughout the intervention and the data will be collected in the CRF and used for final statistical analysis. No conflicts of interest with the sponsors or researchers exist.

